## Discussion

4.

At present, the etiology and pathogenesis of MMD are unknown, and there are no effective therapeutic drugs. The main purpose of treatment in MMD is to improve cerebral blood flow, and extracranial and intracranial revascularization surgery is an effective mean to improve cerebral blood circulation and reduce the risk of secondary strokes (18). EDAS contributes to the formation of collateral vessels in patients with MMD. However, the mechanism of collateral vessel formation after EDAS is still unclear, which leads to a lack of interventions to promote the formation of collateral networks and accelerate the speed of blood flow reconstruction.

Earlier, we found that some patients with MMD have poor development of collateral vessels after EDAS. In our previous study, cerebral artery angiography was performed at 6 months after EDAS, and the Matashima grading of collateral vessel formation was applied to patients, among which 54.2–78.4% had good collateral circulation (grade A or B) and 21.6–45.8% had poor collateral circulation (grade C) (19). Therefore, there is an urgent need for safe and effective drugs to promote the formation of bridging arteries after EDAS and further improve the therapeutic effect of revascularization.

Compared with other statins, atorvastatin calcium tablets have the advantage of stronger regulation of dyslipidemia, shorter half-life, and higher bioavailability (20). Atorvastatin has been widely used in cardiovascular and cerebrovascular diseases as a lipid-lowering and plaque stabilizing drug. Additionally, atorvastatin can promote angiogenesis in stroke and brain injury models (21–23). However, to the best of our knowledge, there have been no reports on the ability of any drug, including atorvastatin, to promote the formation of collateral vessels after EDAS in patients with MMD.

First, since there is no previous study on the efficacy of statins in the treatment of MMD, the dose of atorvastatin used in this study is based on to earlier studies in other neuronal diseases, which means this may not be the optimal dose for patients with MMD. In addition, stratified randomized design will not be carried out in this study. The consistency of baseline characteristics and Suzuki stage of patients in the two groups can only be verified by concordance correlation coefficient, and there may be potential deviations in the results.

In conclusion, we expect to provide new therapeutic options for medically-assisted treatment of MMD by conducting a prospective double-blind randomized controlled study on the formation of collateral blood vessels after statin-induced vascular reconstruction surgery. These results will provide a valuable theoretical basis for larger multi-center clinical trials in the future.

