### Randomization and treatment allocation

2.3.

All enrolled patients will be randomly assigned to the atorvastatin treatment group or the placebo control group in a 1:1 ratio (*n* = 90 for each). The randomization sequence will be obtained according to the SPSS software program, and the randomization process will not be stratified. The randomized sequences of group assignments are then hidden in sequentially numbered opaque, closed envelopes. Atorvastatin (Pfizer) and placebo will be stored at the participating hospitals (20–30°C, while avoiding direct lighting), and they will be handled exclusively by the study nurses responsible for drug storage, distribution, and documentation. Placebo tablets are made from dextrin and have the same weight and appearance as atorvastatin. Two types of tablets are made by Shandong ARURA Pharmaceutical Research and Development Co., based on a randomized sequence, and are numbered sequentially. The randomization information and drug type are not publicly available to all investigators, competent physicians, and patients. All patients will be numbered sequentially, and the 8-week dose will be dispensed by the medication nurse in numbered order. At the end of the follow-up visit for the last enrolled patient, the sealed, opaque envelope will be opened by the principal investigator with unblinding (11).

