### Statistical analysis

3.3.

All data will be analyzed by intention-to-treat and per-protocol. Categorical variables will be analyzed by chi-square test and continuous variables will be compared by independent *t*-tests or ANOVA. A U-test will be performed for variables that do not follow a normal distribution. Univariate analysis will be used to assess age, sex, initial symptoms at diagnosis, collateral grade, posterior circulation involvement, and use of atorvastatin. Variables significantly associated will be selected and analyzed by multiple linear regression. A value of *p* < 0.05 will be considered statistically significant. SPSS 26.0 software will be used for statistical analysis of all data.

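### The Discussion names a concordance correlation coefficient as the only check of baseline and Suzuki-stage balance, but it cannot compare two unpaired arms, and Suzuki stage is not among the listed covariates

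*Protocol article*

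**What the plan says.** Section 2.3 (Randomization and treatment allocation) has patients "randomly assigned to the atorvastatin treatment group or the placebo control group in a 1:1 ratio", 90 per arm, and states that "the randomization process will not be stratified". It describes no matching or pairing. The Discussion repeats that a "stratified randomized design will not be carried out in this study". It then says of the comparability of the arms at baseline that "Suzuki stage of patients in the two groups can only be verified by concordance correlation coefficient", and accepts that the results may deviate because of this.

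Section 3.3 (Statistical analysis) gives the methods: "Categorical variables will be analyzed by chi-square test and continuous variables will be compared by independent" t-tests or ANOVA, with a U-test for non-normal variables. For modelling it says: "Univariate analysis will be used to assess age, sex, initial symptoms at diagnosis, collateral grade, posterior circulation involvement, and use of atorvastatin". It continues: "Variables significantly associated will be selected and analyzed by multiple linear regression". Suzuki stage appears nowhere in section 3.3. Its only mention in the article is in the limitations paragraph.

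**The concern.** The concordance correlation coefficient answers how closely two measurements of the same subject agree, for example two readers grading one angiogram. Patient 1 on atorvastatin has no counterpart on placebo, so there is nothing for the coefficient to agree about.

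The article raises Suzuki stage because allocation is unstratified, then names a check that carries no information about it. A reader given a value near zero could take the arms to be incomparable. A reader given a high value from sorted lists could take them to be well matched. Neither inference would be justified. The listed covariates also leave out the one factor that the limitation names.

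**Working it through.** **1. The plan's own figure.** Section 3.2 uses 79.1% v 58.2%, alpha 0.05 and power 0.80. With a pooled-variance, two-sided test and no continuity correction, the mean rate is 0.6865 and

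n = [1.960 × √(2 × 0.6865 × 0.3135) + 0.842 × √(0.791 × 0.209 + 0.582 × 0.418)]² / 0.209² ≈ 76.2, so 77 per arm.

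Then 154/0.9 = 171.1, so 172 in total. Both figures reproduce. Power is 80.4% at 77 per arm and 86.2% at 90 per arm. Nothing below changes them.

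**2. Why the coefficient fails.** It is

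CCC = 2·cov(x, y) / [var(x) + var(y) + (mean x − mean y)²].

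The numerator needs pairs. If unrelated patients are paired at random, the covariance has expectation 0, and so the coefficient centres on 0. A difference in mean stage enters only through the denominator, where it pulls a value already near 0 still closer to 0. With 90 arbitrary pairs and balanced arms the SD is about 1/√90 = 0.105, giving a 95% range of about ±0.21.

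**3. Simulation.** Two independent arms of 90 with a six-level stage, 4,000 runs. The stage distributions are assumptions; the article gives none.

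| Arms | Mean absolute standardised difference | Mean CCC | 95% range |
|---|---|---|---|
| Same distribution | 0.12 | -0.00 | -0.21 to 0.20 |
| Grossly different | 1.04 | 0.00 | -0.14 to 0.14 |

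The standardised difference separates the two situations clearly. The coefficient does not.

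**4. Dependence on order.** Two arms with exactly the same stage counts gave -0.01 when shuffled, 1.00 when both were sorted, and -0.92 when one was sorted in reverse.

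**5. The covariate list.** Section 3.3 names age, sex, initial symptoms, collateral grade, posterior circulation involvement and atorvastatin. Collateral grade cannot be read as Suzuki stage: the only collateral grade that the article defines is the postoperative Matsushima grade in section 2.5.2, which is the primary outcome.

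**6. What adjustment would gain.** Simulated power with 81 per arm (90 × 0.9) and 79.1% v 58.2%, unadjusted v logistic adjusted:

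| Assumed prognostic OR | 3,000 trials | 4,000 trials |
|---|---|---|
| 3 | 0.822 v 0.844 | 0.820 v 0.838 |
| 5 | 0.838 v 0.876 | 0.819 v 0.864 |

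The gains are 2.2 and 1.8 points at OR 3, and 3.8 and 4.5 points at OR 5. The Monte Carlo standard error of each estimate is about 0.7 points with 3,000 trials (√(0.82 × 0.18/3000) = 0.007), so the gains are approximate.

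**7. How large chance imbalance could be.** Assume a 50% late-stage share. The between-arm difference has SD √(0.25 × 2/90) = 0.0745. It exceeds 10 points in 18% of trials (z = 1.34) and 15 points in about 4% (z = 2.01). If stages differ by 20 to 30 points in A/B rate, also assumed, a 10-point imbalance shifts the effect by 2.0 to 3.0 points and a 15-point imbalance by 3.0 to 4.5 points, against the planned 79.1 − 58.2 = 20.9.

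**The case against.** The strongest reply is that nothing depends on the sentence. It stands in the limitations text, not in section 3.3, and no analysis is defined by it. Section 3.3 already offers valid between-group methods. This stands, and it limits the weight of the point. It does not make the sentence right: the article names a specific method and calls it the only one, so this is a wrong statement rather than a detail left to an analysis plan.

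A reader might infer that the trial's protection against imbalance has failed, or that the primary result will be biased. The documents do not support that. Randomisation protects the comparison, and a baseline check does not. Absence of stratification does not invalidate the test. The imbalances in step 7 of the working are ordinary sampling variation, already covered by the error rate of the unadjusted test, and deleting the coefficient would change none of them. The 15-point case is also a rare one.

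A reader might also infer that Suzuki stage will never be adjusted for. The article shows only that section 3.3 does not list it. The analysis plan is not shown and could add it. Nor is Suzuki stage the article's sole worry: the sentence speaks of baseline characteristics generally and names Suzuki stage as the one example.

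Finally, an added logistic model is more than a wording change. It reports a conditional odds ratio, whereas section 3.2 sizes the trial on a comparison of rates. This also stands, and it is why the model belongs beside the chi-square comparison and not in its place.

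**Conclusion.** The point holds in a limited form. The concordance correlation coefficient is undefined for two unpaired arms until patients are paired arbitrarily. It then reflects listing order and cannot tell balance from imbalance. This follows from the formula and needs no assumption about the patients; the simulation only illustrates it. Calling it the only means of verification contradicts section 3.3.

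The consequence is modest. The validity of the primary test and the sample size of 77 per arm (172 in total, 180 planned) are untouched. Listing Suzuki stage as a fixed covariate is a recommended improvement, not the repair of an invalid analysis. Its benefit of about 2 to 4 power points applies to the adjusted model alone and rests on an assumed prognostic odds ratio of 3 to 5. The documents give neither the prognostic strength nor the distribution of Suzuki stage.

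**What to change.** 1. Delete the concordance correlation coefficient from the Discussion. State that baseline characteristics, including preoperative Suzuki stage, will be tabulated by arm with standardised differences. This costs only wording.

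2. Add to section 3.3, before unblinding, text such as: *In addition to the chi-square comparison of grade A/B rates, a logistic regression of grade A/B on treatment will be fitted with preoperative Suzuki stage as a fixed covariate, included whatever its univariate significance.* Fix the coding of stage at the same time.

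No new data are needed, because the Abstract says that every enrolled patient routinely has DSA before surgery. The cost is reading the stage from those images and reporting one further model, whose conditional odds ratio should be labelled as such and kept apart from the difference in rates.

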## Ethics statement

The studies involving human participants were reviewed and approved by Chinese PLA general Hospital. The patients/participants provided their written informed consent to participate in this study.
